# Effects of early, combined endurance and resistance training in mechanically ventilated, critically ill patients: a study protocol for a randomised controlled trial

**DOI:** 10.1186/s13063-016-1533-8

**Published:** 2016-08-15

**Keywords:** Physiotherapy, Physical function, Intensive care, Mechanical ventilation, Rehabilitation, Weakness, Critical illness

## Abstract

**Background:**

Prolonged need for intensive care is associated with neuromuscular weakness, termed Intensive Care Unit Acquired Weakness. Those affected suffer from severe functional impairment that can persist for years. First studies suggest a positive effect of physiotherapy and early mobilisation. However, the ideal intervention for a preferential functional outcome is not known. So far no randomised controlled trial has been conducted to specifically evaluate an early endurance and resistance training in the mechanically ventilated, critically ill patient.

**Methods/design:**

A randomised controlled trial with blinded assessors and 6-month follow-up will be conducted in a tertiary, interdisciplinary intensive care unit in Switzerland. Participants (*n* = 115; expected dropouts: *n* = 15) will be randomised to a control group receiving standard physiotherapy and to an experimental group that undergoes early mobilisation combined with endurance and resistance training. The inclusion criteria are being aged 18 years or older, expected mechanical ventilation for more than 72 h and qualitative independence before the illness.

Primary endpoints are functional capacity (6-Minute Walk Test) and the ability to perform activities of daily living (Functional Independence Measure) measured at hospital discharge. Secondary endpoints include muscle strength (Medical Research Council sum score, handgrip strength and handheld dynamometry for quadriceps muscle), joint contractures (range of motion), exercise capacity (Timed ‘Up & Go’ Test) and health-related quality of life (Short Form 36). Safety will be monitored during interventions by indirect calorimetry and continuous intensive care standard monitoring. All previously defined adverse events will be noted. The statistical analysis will be by intention-to-treat with the level of significance set at *p* < 0.05.

**Discussion:**

This prospective, single-centre, allocation-concealed and assessor-blinded randomised controlled trial will evaluate participant’s function after an early endurance and resistance training compared to standard care. Limitations of this study are the heterogeneity of the critically ill and the discontinuity of the protocol after relocation to the ward. The strengths lie in the pragmatic design and the clinical significance of the chosen outcome measures.

**Trial registration:**

German Clinical Trials Register (DRKS): DRKS00004347, registered on 10 September 2012.

## Background

Intensive care unit (ICU) survivors have a persistently high mortality and an exceedingly poor quality of life that manifests itself up to 5 years after ICU discharge [1]. Further burdens include exercise limitation, physical and psychological complications as well as increased costs and use of health care services [2]. To outline these multiple long-term consequences after survival of a critical illness the term post intensive care syndrome (PICS) has been agreed on [3]. Consequently, PICS describes impairments in physical, cognitive or mental health status subsequent to a critical illness and persisting beyond hospital discharge.

### Intensive Care Unit Acquired Weakness (ICUAW)

Neuromuscular dysfunctions are an important aspect of the physical impairment following ICU stay and are probably a crucial contributor to the associated long-term disability. They are common in critically ill patients requiring more than 1 week of mechanical ventilation and have an approximate incidence of 40 % [4]. A simple framework to diagnose and classify these neuromuscular disorders has been proposed [5]. Hence, the term ‘Intensive Care Unit Acquired Weakness’ (ICUAW) describes a clinically detected weakness in critically ill patients with no plausible aetiology except for the critical illness itself. ICUAW is associated with worse outcomes such as prolonged weaning from mechanical ventilation [6], weaning failure with a high occurrence of reintubation or tracheotomy [7], longer ICU and hospital stays [8], increased ICU and hospital mortality [9], increased mortality 180 days after ICU discharge [10] in addition to poor functional status, persistent disability in activities of daily living, reduced walking ability and lower quality of life up to 1 year after ICU discharge [11–14] The underlying pathophysiological mechanisms of ICUAW are complex and poorly understood. Several risk factors, in particular, high severity of illness with multiorgan failure, hyperglycaemia and immobilisation, contribute to the development of ICUAW [15]. The process of muscle wasting begins during the first week of a critical illness and thus commences very early and rapidly [16]. So far there is no specific treatment for ICUAW. However, the potential benefit of early rehabilitation and physiotherapy has been suggested by a recent Cochrane review [17].

### Rehabilitation in intensive care

Physiotherapists are seen as an essential part of the multidisciplinary ICU team [18]. Compared to other health care professionals they can be more successful in facilitating early mobilisation and rehabilitation in critically ill patients [19]. Their specific knowledge of neurological and musculoskeletal conditions enables the physiotherapist to assess current rehabilitation needs, to detect early deficits, such as ICUAW, and to set rehabilitation goals accordingly [18]. Consequently, physiotherapists seem ideal to meet the recommendations of the National Institute for Health and Care Excellence (NICE) for an individualised, structured rehabilitation programme with frequent follow-up reviews during critical illness [20]. However, there are only a few randomised controlled trials to support this statement. One randomised controlled trial was conducted by Burtin and colleagues in a medical and surgical ICU and involved 90 patients with a prolonged ICU stay [21]. Participants were randomised into standard physiotherapy alone and standard physiotherapy plus an additional bed cycling training 5 days a week. At hospital discharge the 6-minute walking distance, isometric quadriceps force and the Physical Functioning score of the Short Form 36 (SF-36) were significantly higher in the cycling group. Similarly, Schweickert and colleagues conducted a randomised controlled trial in a medical ICU with 104 mechanically ventilated patients [22]. They found that physiotherapy, specifically very early exercise and mobilisation, during periods without sedation led to more patients returning to functional independence at hospital discharge compared to usual care, and led to fewer days with delirium and mechanical ventilation. However, another randomised controlled trial with 150 participants comparing usual care to intensive exercise that started 5 days after ICU admission, continued during the stay in the ward and for 8 weeks in an outpatient setting, failed to show any benefit for intensive exercise therapy [23]. Finally, a randomised controlled trial, including 50 patients with sepsis syndrome, compared an individualised physical rehabilitation programme starting within 48 h after sepsis diagnosis to standard care without active rehabilitation [24]. There was no significant difference in physical function at ICU discharge, but individuals in the intervention group reported an improvement in physical function and physical role 6 months after hospital discharge on the SF-36.

Given the discrepancies of the findings in the previous few studies, further research to evaluate the long-term outcome of early rehabilitation interventions seems necessary. Future studies should be performed with high methodological quality and report the administered frequency, intensity and timing of the interventions [17, 25]. To our knowledge no randomised controlled trial has so far been conducted to evaluate the efficacy of early physiotherapeutic interventions, including both an endurance and resistance component, in the mechanically ventilated, critically ill patient. Aerobic and strength training are widely recommended and are effective interventions in chronic diseases and disabilities like stroke [26], chronic heart failure [27], older adults’ disabilities [28], chronic obstructive pulmonary disease [29] and cancer-related fatigue [30]. We expect a similar benefit in critical illness. To avoid the limitations of previous studies, we aim to include participants from a general ICU population, containing patients at risk of a prolonged ICU stay and ICUAW as a consequence. Also, and because ICUAW develops early and rapidly, the goal is to start early with low-intensity exercise that will be increased according to the patient’s level of tolerance until full mobilisation.

### Study purpose

This study aims to investigate the effects and safety of an early endurance and resistance training combined with early mobilisation in comparison to standard care in critically ill, mechanically ventilated adults at an interdisciplinary, tertiary ICU.

### Hypotheses

The primary hypothesis is that critically ill, mechanically ventilated adults who participate in an early endurance and resistance training, combined with early mobilisation, have an improved functional capacity and are, therefore, more functionally independent at hospital discharge compared to patients receiving the usual physiotherapy care. Secondary hypotheses are that this early training is as feasible and as safe as standard therapy. Further, we expect improvements in muscle strength at ICU discharge, fewer joint contractures, less time on mechanical ventilation, a shorter length of stay in the ICU and the hospital, and a higher quality of life at 6 months after hospital discharge compared to patients receiving usual care.

## Methods and design

We will conduct a prospective, single-centre, allocation-concealed and assessor-blinded randomised controlled trial with superiority design and 6-month follow-up. The study has been approved by the Ethics Committee of Canton Bern (KEK), Switzerland and is registered in the German Clinical Trials Register (DRKS00004347). This trial adheres to the recommendations from the Consolidated Standards of Reporting Trials (CONSORT) statement [31] (Fig. 1) and is conducted according to Swiss law and Good Clinical Practice (GCP) guidelines.

**Fig. 1 Fig1:**
[figure not shown]
Study flow diagram (CONSORT) [31]. Legend: RCT, randomised controlled trial

### Study population

The study is being conducted in the tertiary, interdisciplinary ICU of the Department of Intensive Care Medicine at the Inselspital, Bern University Hospital. To be eligible to participate in the study patients must be aged 18 or older, be expected to stay on mechanical ventilation for at least 72 h, which reflects a prolonged stay at our unit, and finally, participants must have been independent in their activities of daily living before the onset of critical illness (verbal statement by their proxy). Patients with prior muscle weakness, such as a preexisting neurological or neuromuscular disease with functional deficits or a prolonged stay in the hospital for at least 10 days prior to the ICU admission, are excluded from the study. Further exclusion criteria are contraindications to cycling (mainly fractures or recent surgical procedures to the lower limbs, acute thrombosis, preexisting open wounds, extracorporeal membrane oxygenation (ECMO) and body weight of more than 150 kg), patients who are already enrolled in another intervention study, patients receiving palliative care, patients with a diagnosis on admission that excludes the possibility of walking at hospital discharge (for example, paraplegia) and lastly patients who do not understand either German or French.

### Standard care (control group)

Participants randomised to the control group will receive usual physiotherapy and ICU standard care, which includes sedation and weaning protocols based on previous publications [32]. Current physiotherapy practice is comparable to the European norm [33] consisting of positioning, respiratory therapy, passive range of movement exercises for nonresponsive patients or active exercises if arousable, and early mobilisation. In order to start as early as possible, physiotherapists screen patients regularly focussing on prevention and treatment of functional and pulmonary impairment. However, subject to our internal procedure, physiotherapy and mobilisation will start after medical prescription. Treatments are based on the therapist’s assessment and are accordingly individually tailored. Sessions will usually take place once daily from Monday to Friday and, if deemed necessary (e.g. severe weakness, intensive rehabilitation and weaning period, retained airway secretion or atelectasis in extubated patients), this includes treatment at the weekend.

### Study intervention (experimental group)

Patients randomised to the experimental group will receive a standardised exercise programme involving early endurance and resistance training that is combined with early mobilisation. The clinician in charge will decide before study inclusion, whether there are any contraindications to include the patient, and during the study, if at any time the treatment should be stopped, e.g. in case of an adverse event (see safety). Therefore, the intervention will be started as soon as it is deemed safe by the treating ICU team and will occur from Monday to Friday and, if deemed necessary, at the weekend. Throughout all activities, progression will be increased successively, depending on an individual’s tolerance and stability. If needed, the physiotherapist will split the delivery of the exercise programme into one or more sessions (Fig. 2). The number of treatments, its content and duration will be noted for both the control and experimental group.

**Fig. 2 Fig2:**
[figure not shown]
Daily physiotherapy screening and step progression (experimental group). Legend: ICUAW, Intensive Care Unit Acquired Weakness

Endurance training will be conducted with a motor-assisted bedside cycle ergometer that allows patients to train in a passive, motor-assisted or active mode from a hospital bed (MOTOmed letto2, Reck-Technik, GmbJ & Co. KG, Betzenweiler, Germany) (Fig. 3). Training intensity has been adapted from a previous study with long-term ICU patients from Burtin and colleagues [21]. Thus, the aim for unresponsive patients will be one passive training of 20 min with a fixed pedalling rate of 20 cycles per minute from Monday to Friday. In the course of cycling, patient’s participation will be prompted verbally and by the integrated MOTOmed ServoCycling feature. After achieving patient’s active partaking, the goal will be to train with motor assistance for at least 20 min on level 0. If this is accomplished, assistance will be gradually decreased and subsequently, resistance level and training period increased until a maximum of 60 min on level 6. Tolerance and stability will be judged by the responsible physiotherapist according to patient’s perceived level of exertion (BORG RPE Scale) [34] and especially in unresponsive patients, exceedence of individually set limits. The training position will be supine with an individually adapted head-of-bed elevation to allow for leg movement and comfort.

**Fig. 3 Fig3:**
[figure not shown]
Early endurance training with a bedside cycle ergometer. Picture: [name], Inselspital, Bern University Hospital

The resistance training will consist of an individually tailored exercise programme as well as standardised exercises for both upper and lower limbs and will train the muscle groups for shoulder flexion, shoulder external rotation, elbow flexion, hip abduction, knee extension and foot dorsiflexion. The resistance will be administered by the therapist or with weights, starting from 450 g. Training intensity will aim to achieve 50 to 70 % of the estimated one-repetition-maximum, with a goal of 8 to 12 repetitions and 2 to 5 sets with at least a 2-min rest between series. If a participant is able to perform the exercises correctly, he will be given a tutorial with pictures in order to train independently with nurses or family members. If unable to perform the exercises, the physiotherapist will use tactile facilitation or passive range of movement for all joints and their possible directions.

If the previous exercises are well-tolerated, bed mobility and sitting upright in bed will be started (Fig. 4). If these are well-tolerated and no contraindications as per medical prescription exist, the treatment will be further advanced to mobilising participants to the bedside. There, balance exercises will be performed or, if needed, support will be provided by the physiotherapist or various assistive equipment. After being able to sit for at least 10 min on the side of the bed, regardless of whether support is needed, participants will be moved into a chair with an individually adapted transfer according to the individual’s resources. The aim during all mobilisations will be to involve the patient as actively as possible to promote independence. While sitting, functional tasks and activities of daily living will be performed and gradually increased to standing and walking exercises.

**Fig. 4 Fig4:**
[figure not shown]
Mobilisation levels (experimental group)

### Safety

To ensure the patient’s safety all vital parameters, particularly heart rate, invasive blood pressure and oxygen saturation, will be continuously monitored and recorded by our Patient Data Management System (PDMS), which is routinely checked by the ICU staff. Furthermore, oxygen consumption, energy expenditure and the respiratory quotient by indirect calorimetry will be obtained 30 min prior to, during and for 15 min after physiotherapy. All adverse events (AE) will be noted. These are defined as any event that occurs during or up to 15 min after physiotherapy and persists despite an intervention or therapy interruption. It includes new haemodynamically relevant arrhythmias or otherwise unstable haemodynamics, oxygenation desaturation under 85 %, a fall or other injury as well as any accidental removals of a tube, catheter or similar devices. We use a qualitative physiological approach instead of strict target numbers, as optimal physiological goals for individual patients vary highly and depend on the underlying clinical condition [32]. If a participant exceeds or fails to exceed his individually set limits, the therapist will discontinue the session for the day and will record the reason. If this happens repeatedly, the principal investigator will withdraw the patient from the study. Serious adverse events (SAE) are defined as death, a life-threatening injury or an extension of the length of hospital stay. All SAEs and AEs will be recorded and reported to the principal investigator, who judges their severity and whether they were study-related. All SAEs will also be reported to the local ethics committee. Finally, all occurring complications related to bed rest, such as atelectasis, pneumonia, decubitus ulcer, thrombosis, contracture, delirium and a confirmed critical illness, polyneuropathy or myopathy, will be judged and recorded daily by the treating physician according to our current standard of care.

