## Discussion

This prospective, single-centre, allocation-concealed and assessor-blinded randomised controlled trial with 6-month follow-up will be the first, to our knowledge, to evaluate both an early endurance and resistance training compared to standard care in the mechanically ventilated, critically ill patient from a general ICU population. Considering the devastating consequences of ICUAW, it is imperative to find interventions that improve function and thereby quality of life. The two chosen primary outcomes, 6MWT and FIM, reflect these important physical impairments of ICUAW, and thus have a high clinical relevance for patients surviving prolonged mechanical ventilation. Therefore, the strengths of this trial lie in the pragmatic design of the early initiation and physiotherapy-driven protocol, the prospective inclusion of patients at risk of prolonged mechanical ventilation and its consequences in the form of ICUAW in a wide general ICU population that will be screened for study recruitment within 12 h after ICU admission and will, therefore, be enrolled very early into the trial, as well as the everyday significance of the chosen outcome measure to the participants up to 6 months after hospital discharge. If the experimental intervention should prove superior to standard care, it will be relatively simple to incorporate the intervention protocol into daily routine so that it can be used elsewhere or for guideline development. Limitations of this study are the heterogeneity of the critically ill and the discontinuity of the protocol after relocation to the other wards within the hospital. Also, due to the trial’s nature, it is impossible to blind the treating physiotherapists, ICU staff and the participants to the intervention. However, the outcome assessors will be blinded to group allocation. Finally, the reporting of adverse events during therapy will depend on the treating physiotherapists, which could lead to missing events. However, physiotherapists have been carefully trained and work closely with the ICU nurse at the bedside. Moreover, all safety parameters will be continuously recorded by the PDMS for further safety analysis.

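### The adverse-event definition leaves out listed events that resolve, and the equal-safety hypothesis has no margin, so a non-significant difference with about 50 patients per arm could not support it

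*Protocol article*

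**What the plan says.** All of this comes from the protocol article.

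- **AE definition (Safety).** An AE must fall within a session or the 15 min after it, and it must be one that "persists despite an intervention or therapy interruption". The text then lists what this includes: new relevant arrhythmia or other unstable haemodynamics, saturation under 85%, and "a fall or other injury as well as any accidental removals of a tube, catheter or similar devices".
- **Serious adverse events (Safety).** These carry no persistence condition: "Serious adverse events (SAE) are defined as death, a life-threatening injury or an extension of the length of hospital stay".
- **Other safety records.** When a participant goes outside individually set limits, "the therapist will discontinue the session for the day and will record the reason" (Safety). Bed-rest complications are recorded daily (Safety). The Discussion adds that "all safety parameters will be continuously recorded by the PDMS for further safety analysis". The Outcome section names the participants' physiological response as a safety outcome alongside AEs.
- **Safety hypothesis (Hypotheses).** A secondary hypothesis is that "this early training is as feasible and as safe as standard therapy".
- **Design and tests.** Methods and design declares superiority. Statistical analysis names Student's t test and the Mann-Whitney U test for comparing the groups, with significance at p < 0.05. Neither section gives a margin or criterion for equal safety.

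**The concern.** There are two separate problems.

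**What is counted.** Persistence is joined to timing by an *and*, so it is a condition of being an AE. A physiological event that ends because the session was interrupted or the patient was treated fails the condition, even when it is of a listed type. For a trial of exercise in ventilated patients, brief desaturation or haemodynamic disturbance during a session is a large part of what a reader wants to know. The condition also fits badly with a fall or a pulled catheter, which happen at one moment. Two therapists could code the same fall differently, and the treating therapists who report AEs are not blinded.

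**What can be concluded.** A claim of equal safety is an equivalence or non-inferiority claim. It needs a margin, or at least an interval to be judged against. A superiority framework with difference tests supplies neither. If few AEs are counted and the comparison is non-significant, the result could be taken as support for the hypothesis when it shows only that the trial is small for this question.

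**Working it through.** **1. The plan's own sample size.** Inputs from Sample size: difference 54 m, SD 81 m, power 80%, alpha 0.05 (two-sided reproduces the figure).

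n per arm = 2 × (1.96 + 0.8416)² × 81² / 54² = 2 × 7.849 × 2.25 = 35.3, so 36, as stated.

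Total = 2 × (36 + 14) + 15 = 115, as stated. The number evaluable is 50 per arm. This calculation concerns the 6-Minute Walk Test only; no event rate, margin or sample size is given for safety.

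**2. Precision for a safety comparison.** The AE rates are my assumptions, because the article gives none. With the same true rate p in both arms and n = 50 per arm, the 95% half-width is 1.96 × √(2p(1−p)/50).

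| Assumed rate | Half-width |
|---|---|
| 5% | 1.96 × √0.0019 = 8.5 points |
| 10% | 1.96 × √0.0036 = 11.8 points |
| 20% | 1.96 × √0.0064 = 15.7 points |

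If all 115 randomised patients were analysed (57.5 per arm on average), each half-width shrinks by √(50/57.5) = 0.933, to about 8.0, 11.0 and 14.6 points. The conclusion does not change.

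**3. Power of a difference test to detect a doubled risk, 50 per arm.** With p̄ the mean of the two rates, power = Φ{[|p₁−p₂| − 1.96√(2p̄(1−p̄)/50)] / √[(p₁(1−p₁)+p₂(1−p₂))/50]}. Because the normal approximation is weak with few events, exact power of Fisher's test is shown beside it.

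| Assumed rates | z test | Fisher |
|---|---|---|
| 5% v 10% | (0.05 − 0.1033)/0.0524 = −1.02; 16% | 6% |
| 10% v 20% | (0.10 − 0.1400)/0.0707 = −0.57; 29% | 20% |
| 20% v 40% | (0.20 − 0.1796)/0.0894 = 0.23; 59% | 52% |

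A true doubling would therefore be non-significant in about 41% to 84% of such trials by z test (49% to 94% by Fisher, from unrounded power).

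**4. What a formal non-inferiority claim would need.** Take an illustrative margin of 10 points (assumed), equal true rates, one-sided 0.025 and 80% power: n per arm = 7.849 × 2p(1−p) / 0.10². This gives 75, 142 and 252 per arm at rates of 5%, 10% and 20%. With 50 per arm the power is 63%, 39% and 24%.

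**5. Effect of the persistence condition.** The share of events that persist is unknown, so a range is shown. Assume the same share in both arms, with the counted patient-level rate falling in proportion, and true rates of 20% v 40%.

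| Share persisting | Counted rates | Power (z test) |
|---|---|---|
| 100% | 20% v 40% | 59% |
| 50% | 10% v 20% | 29% |
| 25% | 5% v 10% | 16% |

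Even a filter that acts equally on both arms shrinks the visible absolute difference and the chance of detecting it.

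**The case against.** The strongest reply is that the AE label is only one part of the safety data. Serious adverse events, daily bed-rest complications, reasons for stopped sessions, calorimetry and continuous monitoring carry no persistence condition, and physiological response is an outcome in its own right. This stands. A reader might infer that the whole safety analysis undercounts harm. The documents do not support that. What is understated is the count of events labelled AEs; transient events may still be recoverable from other records.

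Second, no section assigns a test to AEs. A t test or Mann-Whitney test would not be the natural choice for a yes/no outcome, and a margin could sit in an analysis plan that is not shown. This also stands. A reader might infer that equal safety will be declared from p > 0.05, but the article does not say so. What can be said is that the stated hypothesis does not match the stated design and tests.

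Third, the wording on falls and device removals is ambiguous rather than flatly contradictory. It can be read as counting every listed event outright, and a removed tube does not put itself back. I accept this, but the coding still needs to be settled.

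Finally, a reader might infer that losses fall mainly in the training arm. That is plausible, but the article has no event data to show it, and control patients also receive active exercise and early mobilisation.

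**Conclusion.** The point holds in two limited parts.

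1. Read as written, the AE definition excludes listed physiological events that resolve on interruption or treatment, and it leaves open whether falls and device removals must persist. How many events this removes cannot be derived from the document.
2. The equal-safety hypothesis has no margin and sits under a superiority design with only difference tests named. With about 50 patients per arm and assumed AE rates of 5% to 20%, the interval for the risk difference is about ±8.5 to ±16 points and power to detect a doubling is about 16% to 59% by z test. A non-significant result would be compatible with a materially higher risk.

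The figures rest on assumed event rates and one yes/no outcome per patient. The walk-test sample size reproduces and is not affected.

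**What to change.** For the safety analysis, without altering any rule for conducting or stopping sessions:

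- Report every occurrence of a listed event during, or up to 15 min after, a physiotherapy session in both arms, whether or not it persisted. Record persistence as an attribute, and state that falls and device removals count as they occur.
- Where events were not noted prospectively, supplement from the monitoring record, checked for artefact, and from the stopped-session reasons.
- Give, by arm, the number of patients with an event and the events per session, with the between-arm difference and 95% confidence interval, allowing for clustering of sessions within patient.
- Reword the safety hypothesis as estimation of the difference with its interval, and state that p > 0.05 will not be taken as equal safety.

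The cost is wording plus derivation from data the article says are already recorded. More events will be listed in both arms, and monitor signals will need artefact review. Recruitment began in October 2012 and was due to end in February 2016, so recovery of transient events in patients already treated will be incomplete, and the report should say so.
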